### Data collection

Demographic and outcome data will be collected from the clinical records and recorded under a unique study identifier number. Basic epidemiologic parameters such as gestational age at birth, birth weight, corrected gestational age, postnatal age and weight at study enrolment, use of antenatal steroids, mode of delivery, doses of surfactant administered, birth plurality and diagnoses at enrolment will be recorded for each infant. Oxygen saturation and FiO_2_ data will be downloaded from the ventilators. Paper data will be stored in a locked filing cabinet. Patient de-identified electronic data will be stored in password-protected computers and on encrypted devices.

### Statistical analysis

Data will be compared between infants in the intervention group (closed-loop automated oxygen control) and infants in the control group (manual oxygen control). The data will be assessed for normality; Student’s *t* test will be used for normally distributed data and Mann–Whitney *U* test for skewed data. Categorical data will be assessed using the Fisher two-tailed exact test. The analysis will be undertaken using SPSS software (SPSS Inc, Chicago, IL, USA). Patients’ data will be analysed according to their randomised assignment group. Imputation of missing data will not be performed.

Ventilation settings and oxygen requirements at the beginning of the study will be compared between infants in the intervention group (closed-loop automated oxygen control) and infants in the control group (manual oxygen control). If there are any statistically significant differences indicating different severities of respiratory disease, we will perform subgroup analysis and comparisons between infants with more and less severe lung disease.

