## Methods

This is a non-blinded, superior, randomised controlled trial. Infants are allocated to parallel groups in a 1:1 ratio.

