### Sample size

In an interim analysis of data from a randomised crossover study on CLAC in ventilated infants born at or above 34 weeks of gestation that was undertaken in our unit, the use of a closed-loop oxygen system was associated with a reduction in the mean FiO_2_ delivery during hyperoxia from 29.6% (manual oxygen control period) to 24.7% (automated oxygen control period, *p* = 0.018), that is a difference of 4.9%. The standard deviation for the FiO_2_ requirement of the infants at the beginning of the automated oxygen control period was 4.7% [14]. Randomisation of 40 infants allowed to detect a difference in the mean FiO_2_ delivery during hyperoxia of 4.9% with a 90% power at the 5% significance level [15].

At the request of the Ethics committee, an interim analysis will be carried out after half the sample have been recruited to review if enough data have been gained at that point. The analysis will be performed by an independent researcher not involved in the project to avoid introducing bias to our data. The research team will be blinded to the results of the interim analysis unless there are any significant findings.

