## Discussion

This study will compare the effectiveness of closed-loop automated oxygen control to manual oxygen control in ventilated infants born at or above 34 weeks of gestation. To date, studies on CLAC have included very preterm or low birth weight infants [8–10, 16–21] and there are limited data on more mature neonates who are also vulnerable to the risks related to oxygen treatment. In a randomised crossover study, we demonstrated that the use of closed-loop automated oxygen control was associated with an increased percentage of time spent in the target oxygen saturation range and reduced time spent in hyperoxaemia, with fewer manual adjustments to the inspired oxygen concentration in ventilated infants born at or above 34 weeks of gestation [14]. In addition, CLAC was more effective in infants with more severe respiratory disease resulting in a larger increase in the time spent in oxygen saturation targets [11]. That study, however, was limited by its crossover design, the limited duration of the monitoring periods and the relatively low supplemental oxygen requirement of our infants. This randomised controlled trial will provide more robust evidence of the effect of CLAC on the duration of oxygen treatment that is related to respiratory morbidity [22] and the length of intensive care stay and therefore may demonstrate if CLAC could improve outcomes for late preterm and term born infants. This will be essential knowledge before the intervention is implemented into standard care.

Several algorithms have been developed for automated oxygen control and it is likely that differences in their design influence their performance. The ‘Oxygenie’ controller used in this study follows a proportional integral derivative (PID) algorithm. In preterm infants on respiratory support, the Oxygenie controller was more effective in keeping oxygen saturations within the target range and preventing hyperoxaemia and hypoxaemia when compared with a hybrid rule-based adaptive controller (CLiO_2_) [23, 24]. The use of an algorithm that most successfully avoids hypoxaemic and hyperoxaemic episodes will increase our ability to detect any differences in the primary outcomes of our study and may further reduce morbidity in our study population.

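### The planned response to baseline imbalance, a significance test followed by severity subgroups, leaves the primary comparison unadjusted; prespecified adjustment for enrolment FiO2 would be sounder at almost no cost

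*Protocol article*

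**What the plan says.** All of this is in the protocol article. The Statistical analysis section compares the arms, by randomised group, with a t test or a Mann–Whitney U test depending on a normality check. It names no covariate. It then adds a baseline step: "Ventilation settings and oxygen requirements at the beginning of the study will be compared between infants in the intervention group" and those in the control group. The consequence is stated next: "If there are any statistically significant differences indicating different severities of respiratory disease, we will perform subgroup analysis and comparisons" of infants with more and with less severe lung disease. That section does not give the threshold for significance. The only level stated is the 5% in the Sample size section.

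The design is parallel ("Infants are allocated to parallel groups in a 1:1 ratio"), so 40 infants give 20 per arm. The Randomisation section describes a generated sequence concealed in envelopes. On severity, the Discussion says of the unit's crossover study that "CLAC was more effective in infants with more severe respiratory disease resulting in a larger increase in the time spent in oxygen saturation targets".

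**The concern.** Under concealed random allocation, any baseline difference between the arms arises by chance. A baseline p-value therefore answers a question whose answer is already known. It does not tell whether an imbalance matters to the outcome. That depends on the size of the imbalance and on how strongly the variable predicts the outcome.

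The rule has three weaknesses:

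- It does nothing about moderate imbalances, which are common at 20 per arm and fall short of significance.
- When it does act, it splits the sample. Splitting gives small comparisons within severity groups and leaves the overall estimate as it was.
- It ties the question of whether the effect varies with severity to whether the arms happen to differ. The two are unrelated.

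At stake is how credible the primary comparison will be in the one trial that is run, should its arms differ in oxygen requirement at entry. Some precision may also be lost, although the baseline data are to be collected anyway.

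**Working it through.** **Inputs.** From the Sample size section: "Randomisation of 40 infants allowed to detect a difference in the mean FiO_2_ delivery during hyperoxia of 4.9" percentage points; SD 4.7 points ("The standard deviation for the FiO_2_ requirement of the infants at the beginning of the automated oxygen control period was 4.7"); "with a 90% power at the 5% significance level". From Methods: 1:1 allocation, so 20 per arm. Assumed: a 5% two-sided threshold for the baseline test, and a correlation ρ between baseline FiO2 and the outcome. The document gives no ρ, so a range from 0 to 0.7 is shown.

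**1. The plan's own figure.** n per arm = 2(1.96 + 1.2816)² × 4.7² / 4.9² = 19.3, rounded up to 20, so 40 in total. The stated size reproduces with a two-sided test. The standardised effect is 4.9/4.7 = 1.04 SD, and the noncentral t distribution with 38 df gives 89.5% power. This effect concerns FiO2 during hyperoxia. The primary outcome is percentage of time with SpO2 > 96%, so power figures based on 1.04 SD only illustrate relative gains and losses.

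**2. What the trigger can see.** The standard error of a standardised baseline difference is √(2/20) = 0.316. The critical value is t(0.975, 38) = 2.024, and 2.024 × 0.316 = 0.64 SD. Anything smaller passes unnoticed. By simulation, about 6.4% of trials would have an imbalance above 0.5 SD that is not significant.

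**3. Behaviour of the unadjusted test.** Simulated with normal data, 20 per arm and no treatment effect. Over all randomisations, mean error is near zero and type I error is about 5% at every ρ. Within trials that have a chance imbalance in the covariate:

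| ρ (assumed) | Mean error after a significant imbalance | Unadjusted type I error, baseline p < 0.05 | Unadjusted type I error, baseline p 0.05–0.20 | ANCOVA type I error, baseline p < 0.05 |
|---|---|---|---|---|
| 0.3 | 0.21 SD | about 9% | about 6.6% | about 5% |
| 0.5 | 0.36 SD | about 18% | about 8.9% | about 5% |
| 0.7 | 0.50 SD | about 32% | about 11.7% | about 5% |

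Repeat runs differ by a few tenths of a point in the p 0.05–0.20 column and by up to about two points in the p < 0.05 column.

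**4. The subgroups.** For an effect of 1.04 SD, a subgroup with 10 per arm has about 60% power and one with 5 per arm about 31%, against 89.5% for the whole trial.

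**5. What adjustment costs or gains.** ANCOVA multiplies the variance of the estimate by roughly (1 − ρ²)(1 + 1/(N − 4)). With N = 40, this equals 1 at ρ = √(1/37) = 0.16. Simulated power at the 1.04 SD sizing effect, against 89.5% unadjusted:

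| ρ | 0 | 0.1 | 0.2 | 0.3 | 0.5 | 0.7 |
|---|---|---|---|---|---|---|
| ANCOVA power | 88.8% | 89.1% | 90.2% | 91.2% | 95.4% | 99.3% |

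**The case against.** The strongest reply is that the primary test is sound as it stands. Randomisation makes the unadjusted comparison unbiased, and its 5% error rate already allows for chance imbalance. The subgroups come after the main comparison and do not replace it, so the primary p-value is the same whether or not the rule fires. This stands, and it limits the weight of the point.

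Some stronger readings are tempting, but the document does not support them:

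- *The primary estimate is biased or confounded.* A reader might infer this. Only error conditional on a chance imbalance is at issue, and adjustment removes it only for the covariate adjusted for.
- *Adjustment must add power.* It does so only above ρ of about 0.16, and no ρ is given. The Discussion notes that oxygen requirements were relatively low in the crossover study. If baseline FiO2 clusters near room air here too, it may predict little.
- *The Discussion shows that severity predicts the primary outcome.* It reports that the effect on time in target differed by severity. That is effect modification on another measure, and it supports looking at severity in its own right.
- *The severity cut-point would be chosen after seeing the data.* The article states none, but a cut-point may sit in the full protocol or analysis plan, so its absence is not held against the plan.
- *The rule will often fire by chance.* With five independent baseline tests the chance is 1 − 0.95⁵ = 23%. The number of tests is not stated, ventilator settings and FiO2 are probably correlated (about 18% at a pairwise correlation of 0.5 and 15% at 0.7), and the rule also requires that the difference indicate different severity.

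The choice of rule is not rescued by any of this. Validity on average does not make a significance gate followed by subgroups a sensible answer to an imbalance in the trial at hand.

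**Conclusion.** The concern holds in a limited form. The planned test is valid on average, but the rule meant to deal with baseline imbalance does not do so. It is silent below about 0.64 SD. Above that, it adds weak subgroup comparisons and leaves the overall comparison uncorrected, with type I error in those trials of about 9% to 32% for ρ from 0.3 to 0.7. Analysis of covariance on the same covariate holds about 5%.

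These figures rest on an assumed ρ, a 5% baseline threshold, one baseline variable and normally distributed data. The power figures also borrow the sizing effect for FiO2 during hyperoxia. The direction of the conclusion does not depend on that effect.

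This is a should-fix point: a cheap improvement to a rule the article states explicitly.

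**What to change.** - Delete the rule that makes further analysis depend on a significant baseline difference. Describe baseline ventilation settings and oxygen requirements by arm, without tests.
- Prespecify the primary analysis of percentage of time with SpO2 > 96% as a comparison of arms adjusted for FiO2 at enrolment (continuous), whatever imbalance is observed. The outcome is a bounded percentage and may be skewed, so use a method that tolerates this, for example a linear model with a permutation p-value and a bootstrap 95% confidence interval.
- Examine severity once and unconditionally, as an exploratory arm-by-baseline-FiO2 interaction.

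The cost is analysis wording and one degree of freedom. No new data are needed, because oxygen requirement at study start is already to be compared and FiO2 is downloaded from the ventilators. The power loss is about one point or less if ρ is below about 0.16.

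One limit remains: adjusting for FiO2 does not correct an imbalance in ventilation settings beyond what FiO2 captures. If the investigators think a ventilation setting is also strongly prognostic, they should name it as a covariate in advance.

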### Safety

All participants will receive standard care and monitoring by clinical staff. Ventilator settings will be adjusted and additional investigations such as blood gases and chest radiographs will be performed at the discretion of the clinicians. Therefore, there should not be any risk imposed to the intervention group with the addition of the closed-loop automated oxygen delivery system. The system does not mask large increased oxygen requirements between manual observation recordings, as it activates an alarm when there is an increase in the oxygen requirement ≥ 30% from the basal level alerting the clinical team. All serious adverse events will be recorded on a serious adverse event (SAE) form and will be emailed to the sponsor within one working day of the Chief Investigator (CI) becoming aware of the event. When the event is unexpected and thought to be related to the use of the device, this will be reported by the CI/Sponsor to the Ethics and Health Research Authority within fifteen days.

### Protocol compliance

A member of the research team will be onsite or contactable after hours to advise and trouble-shoot and promote adherence to the protocol. Any accidental protocol deviations will be appropriately documented and reported to the Chief Investigator and Sponsor immediately. The Chief Investigator and sponsor will monitor and audit the conduct of this research.

## Research Ethics Committee (REC) and other regulatory review and reports

Before the start of the study, a favourable opinion was sought from a REC for the study protocol and other relevant documents (informed consent forms and patient information leaflets).

### Regulatory review and compliance

For any amendment to the study, the Chief Investigator or designee, in agreement with the sponsor will submit information to the appropriate body in order for them to issue approval for the amendment.

### Data protection and patient confidentiality

The General Data Protection Regulation and Data Protection Act 2018 will be adhered to. Data will be de-identified before being entered in a secure database. A unique study identifier number will be issued to each participant on enrolment into the study. That number will be used in all subsequent data collection forms. Patient paper data will be stored in a locked filing cabinet in a room that is only accessible to the research team and that is based at the Neonatal Intensive Care Unit facilities at King’s College Hospital. Patient de-identified electronic data will be stored on encrypted university computers or memory stick devices, both of which require a user identification and password verification.

### Archiving

At the end of the trial, all essential documentation will be archived securely by the CI for a minimum of 25 years from the declaration of the end of the trial. Essential documents include those which enable both the conduct of the trial and the quality of the data produced to be evaluated and show whether the site complied with all applicable regulatory requirements. All archived documents will continue to be available for inspection by appropriate authorities upon request.

### Indemnity

King’s College London indemnity applies for insurance/indemnity to meet the potential legal liability of the sponsor for harm to participants arising from the design and management of the research. NHS indemnity scheme applies for insurance/indemnity to meet the potential legal liability of the investigators arising from harm to participants in the conduct of the research.

### Access to the final study dataset

The individuals in the study will be notified of the outcome of the study as below. The investigators will have access to the final study dataset. Participants will be informed that anonymised data may be shared with other researchers for research purposes only.

### Dissemination policy

On completion of the study, the data will be analysed and a final study report will be prepared that could be accessed via the sponsor. The study will be presented at research meetings at the Neonatal Intensive Care Unit at King’s College Hospital as well as university meetings at King’s College London. Anonymised study data will be presented at conferences and published by the investigators in peer-reviewed journals. Participants will be notified of the outcome of the study via the provision of the publication and an accompanying newsletter.

### Intellectual property

All intellectual property rights and know-how in the protocol and in the results arising directly from the study shall belong to KCL.

## Discussion

This study will compare the effectiveness of closed-loop automated oxygen control to manual oxygen control in ventilated infants born at or above 34 weeks of gestation. To date, studies on CLAC have included very preterm or low birth weight infants [8–10, 16–21] and there are limited data on more mature neonates who are also vulnerable to the risks related to oxygen treatment. In a randomised crossover study, we demonstrated that the use of closed-loop automated oxygen control was associated with an increased percentage of time spent in the target oxygen saturation range and reduced time spent in hyperoxaemia, with fewer manual adjustments to the inspired oxygen concentration in ventilated infants born at or above 34 weeks of gestation [14]. In addition, CLAC was more effective in infants with more severe respiratory disease resulting in a larger increase in the time spent in oxygen saturation targets [11]. That study, however, was limited by its crossover design, the limited duration of the monitoring periods and the relatively low supplemental oxygen requirement of our infants. This randomised controlled trial will provide more robust evidence of the effect of CLAC on the duration of oxygen treatment that is related to respiratory morbidity [22] and the length of intensive care stay and therefore may demonstrate if CLAC could improve outcomes for late preterm and term born infants. This will be essential knowledge before the intervention is implemented into standard care.

Several algorithms have been developed for automated oxygen control and it is likely that differences in their design influence their performance. The ‘Oxygenie’ controller used in this study follows a proportional integral derivative (PID) algorithm. In preterm infants on respiratory support, the Oxygenie controller was more effective in keeping oxygen saturations within the target range and preventing hyperoxaemia and hypoxaemia when compared with a hybrid rule-based adaptive controller (CLiO_2_) [23, 24]. The use of an algorithm that most successfully avoids hypoxaemic and hyperoxaemic episodes will increase our ability to detect any differences in the primary outcomes of our study and may further reduce morbidity in our study population.

Participants are enrolled in our study within 24 h of initiation of mechanical ventilation. This limits the time frame to approach parents and obtain informed consent on participation but will provide more data points available for analysis as the duration of mechanical ventilation in infants born at or near term may be relatively short.

Previous studies investigating compliance with achievement of SpO_2_ targets showed that caregivers are more concerned to prevent hypoxaemia than hyperoxaemia with higher percentages of time spent above oxygen saturation targets [6, 25, 26]. Exposure to hyperoxia can lead to the generation of free radicals that induce membrane disruption and activate inflammatory pathways through lipid peroxidation, affecting multiple organ systems [27]. In addition, free radicals, as shown in animal studies, can activate several enzymes and vasodilators in the nitric oxide pathway promoting pulmonary vasoconstriction and resulting in persistent pulmonary hypertension of the newborn (PPHN) [28]. Newborn infants have reduced antioxidant capacity and they are particularly susceptible to the hyperoxic injury related to oxidative stress [29, 30]. Therefore, compliance with achievement of oxygen saturation targets and avoiding hyperoxaemia are important in near-term or term-born infants.

In conclusion, if this study demonstrates that CLAC reduces hyperoxia and the overall duration of oxygen treatment in more mature infants, that could help improve clinical outcomes and reduce morbidity in this population.

## Trial status

At the time of submission, this trial has been approved by the NHS Research Ethics Committee and the Health Research Authority (Protocol version 1.2, 10/11/2022). Recruitment of participants started on 01/12/2022 and will be completed by 30/11/2023.

## Data Availability

[name] will have access to the final trial dataset. There are no contractual agreements that limit such access for all four investigators.

## Abbreviations

CI: Chief Investigator
CLAC: Closed-loop automated oxygen control
FiO2: Fraction of inspired oxygen concentration
HFOV: High-frequency oscillatory ventilation
HRA: Health Research Authority
KCH: King’s College Hospital
KCL: King’s College London
PID: Proportional-integral-derivative
PPHN: Persistent pulmonary hypertension of the newborn
ROP: Retinopathy of prematurity
REC: Research ethics committee
SAE: Serious adverse event
SpO_2_: Oxygen saturation levels
